### Ethics Approval and Consent to Participate Statement

The participants of this study are minors. This intervention study does not involve administering the HPV vaccine but focuses on raising awareness. The research team will inform parents about the study via an information leaflet distributed in June and August, and written consent will be obtained unless parents object.

The sponsor and the investigator(s) commit to conducting this research in compliance with French law number 2012-300 of March 5, 2012, relating to research involving human participants, as well as in accordance with Good Clinical Practice (International Council for Harmonisation, version 4, November 9, 2016; and decision of November 24, 2006) and the Declaration of Helsinki (full text available online [22]).

The research will be conducted in accordance with the present protocol. Except in emergency situations requiring the implementation of specific therapeutic procedures, the investigator(s) commit(s) to fully comply with the protocol, particularly with respect to obtaining consent and the reporting and follow-up of serious adverse events.

Data collected during this research will be processed by the Centre Hospitalier Universitaire de La Réunion in compliance with the French Data Protection Act no. 78-17 of January 6, 1978, as amended by Act 2004-801 of August 6, 2004.

Approval from the ethics committee and the data protection authority is currently in progress.

### Patient and Public Involvement

Following the distribution of information leaflets to parents and students, and after obtaining consent from school directors, the schools will be randomized. The research team, together with teachers, will verify any potential objections and ensure that students whose parents object do not participate in the interventions. Parents may withdraw their child from the study at any time by simple request. Participants will have the right to receive information about the study, including the results.

### Sample Size

This is a cluster randomized controlled trial with 3 parallel arms, designed to evaluate the effectiveness of 2 awareness programs addressing HPV-related risks and its prevention in seventh-grade classes in Réunion colleges. The reference arm is a no-intervention group. The allocation ratio is 1:1:1. The primary outcome is the proportion of students who initiate the HPV vaccination schedule. The World Health Organization Strategic Advisory Group of Experts has recently reviewed evidence indicating that a single-dose vaccination schedule provides effectiveness comparable to the traditional 2-dose schedule.

The research team may include up to 1 additional ambassador class in arm 2 if a college has more than 5 seventh-grade classes, to facilitate information dissemination (Figure 2).

**Figure 2 figure2:**
[figure not shown]
Diagram showing the composition of colleges randomly assigned.

To calculate the required number of participants, the following assumptions are considered:

It is hypothesized that, by the end of the school year, 30% of students in the control group will have initiated vaccination. This estimate is based on vaccination coverage data published by Santé Publique France in 2023, which reported that 21.5% of children (girls and boys combined) aged 12 in Réunion had received at least one dose of the HPV vaccine by December 31, 2023 [23].It is hypothesized that the ambassador classes and the serious game will increase coverage to 45% in the respective intervention groups.A constant intracluster correlation coefficient of 0.1, considered a rather conservative value [24].An α risk of 5%90% powerThe average number of seventh-grade students (n) is 190 per college.A design effect (allowing intraclass correlation [ICC] to be taken into account) of 19.9, which is calculated as 1 + ICC × (n – 1).

Therefore, a total of 8 colleges per arm will be included, resulting in 24 colleges overall and approximately 3144 students.

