**Methods:**

This protocol describes the design of a randomized, open-label, controlled trial aimed at evaluating the effectiveness of 2 awareness-raising interventions—peer learning and a card-based serious game—in improving HPV vaccination rates among middle school students in Réunion Island. The study will span an entire school year, beginning in August. Approximately 3600 students from 24 middle schools in Réunion Island will be included, with schools randomized into 3 groups of 8 each: (1) a control group receiving the existing national vaccination campaign initiated by the French public health institute; (2) ambassador classes, whose students will receive education about the HPV vaccine and later educate other students in the same school; and (3) serious game card group, where students can play and learn about HPV during a science class. The primary outcome will be the proportion of teenagers who initiate the vaccination process, compared across the 3 groups using appropriate statistical methods. Anonymized data will be collected at the end of the school year using social security records. Teenagers’ knowledge of HPV will be assessed both before and 3 months after each intervention, and satisfaction will also be evaluated after the intervention in each group.

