### Statistical Analysis

Analyses will be performed by the biostatistics team at La Réunion University Hospital, in collaboration with the study methodologist and coordinating investigator, according to the statistical analysis plan established before database lock. Analyses will be conducted using SAS (version 9.4; SAS Institute Inc), Stata (version 16; StataCorp), or R (R Foundation) software.

Qualitative variables will be described using counts and percentages. Quantitative variables will be summarized using the mean and SD, or the median and range, as appropriate.

Comparative analyses of the end points will be conducted according to the intention-to-treat principle, meaning that students will be analyzed in the group to which their class was randomized, regardless of any deviations from the research protocol. All students included and followed until the end of the school year will be considered in the analysis.

At the college level, the main deviation from the expected research protocol is nonparticipation in the intervention allocated by randomization.

At the student level, expected deviations from the protocol include occasional absenteeism during data collection at different periods, permanent departure from college during the academic year, or individual refusal to participate at any point during the study. These factors may lead to a loss of statistical power and could affect the generalizability of the findings. Statistical significance will be set at *P*<.05 (2-sided).

The results of this study will be published in accordance with the CONSORT (Consolidated Standards of Reporting Trials) recommendations extended to cluster randomized trials.

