### Study Strengths

To the best of our knowledge, this study is the first of its kind in France, enhancing the program recently launched by the French government for the 2023 school year by incorporating innovative educational tools, such as serious games, in comparison with peer learning through ambassador classes. The results of this study, along with the development of these educational programs, could be adapted and applied to other regions in France—or even to other countries—for different medical subjects.

In addition, the sample size allows us to achieve a higher level of confidence.

This study focuses on a major public health issue in the current epidemiological context. It is important to address this now, given the effectiveness of the vaccine in preventing papillomavirus-related complications. The study will help identify the life stage during which vaccination is most effective and guide targeted primary prevention efforts.

If this study demonstrates effectiveness, the expected impact will be significant, providing numerous benefits for public health in the short, medium, and long term:

Validate the most effective strategies for improving HPV vaccination campaigns in French schools and potentially internationally.Increase HPV vaccination coverage in Réunion Island.Optimize school-based vaccination campaigns.Promote the involvement of students in the HPV vaccination campaign across all Réunion colleges.Enhance and reinforce the messages delivered by health care professionals and public communication channels.Raise awareness among the families of participating children.Reduce the incidence of HPV-related benign conditions, such as condyloma, as well as precancerous and cancerous lesions.

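### The stated sample-size assumptions require 23 colleges per arm, not 8; with 8 the power per comparison is about 44-49%, not 90%, and the student totals conflict

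*Protocol article*

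**What the plan says.** The assumptions are listed in Methods, Sample Size, below Figure 2. For the control arm, "by the end of the school year, 30% of students in the control group will have initiated vaccination". For the two interventions, "the ambassador classes and the serious game will increase coverage to 45% in the respective intervention groups". Clustering enters through "A constant intracluster correlation coefficient of 0.1, considered a rather conservative value", an average of 190 seventh-grade students per college, and a design effect of 19.9. The error rates are alpha 5% and power 90%. The Statistical Analysis section makes the test two-sided ("Statistical significance will be set at *P*<.05 (2-sided").

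The section then concludes: "Therefore, a total of 8 colleges per arm will be included, resulting in 24 colleges overall and approximately 3144 students".

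The Abstract gives another size for the same set of schools: "Approximately 3600 students from 24 middle schools". Expected Outcomes repeats the 30% and 45% figures and says that the 45% target was used for the sample size. Study Strengths presents the size as an advantage: "In addition, the sample size allows us to achieve a higher level of confidence".

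**The concern.** Every input to a standard cluster sample-size calculation is given, so the result can be checked without assuming anything. An ICC of 0.1 with 190 students per college multiplies the required number almost twentyfold. A 15-point difference between 30% and 45% is too small for 8 colleges per arm to be a plausible answer at 90% power. The student totals raise a second doubt, because neither equals 24 times the 190 used in the design effect.

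The claim that 90% power is available for the target effect is at stake. If true power is near one half, a real gain of 15 points is about as likely to be missed as found. Readers who trust the stated power would then give a non-significant result more weight than it can bear.

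**Working it through.** **Inputs** (Methods, Sample Size; sidedness from Statistical Analysis): p₀ = 0.30, p₁ = 0.45, two-sided alpha 0.05, power 0.90, ICC = 0.1, m = 190 per college, three arms at 1:1:1.

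**1. Design effect.** 1 + 0.1 × (190 − 1) = 19.9. The plan's figure is reproduced.

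**2. Students per arm before clustering.** With unpooled variance, n = (1.960 + 1.282)² × (0.30 × 0.70 + 0.45 × 0.55) / 0.15² = 10.507 × 0.4575 / 0.0225 = 213.7. With pooled variance under the null, n = 216.8.

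**3. Colleges per arm.**
- Unpooled: 213.7 × 19.9 ≈ 4252; 4252 / 190 = 22.4.
- Pooled: 216.8 × 19.9 ≈ 4315; 4315 / 190 = 22.7.

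Both round up to 23. The plan's figure of 8 is not reproduced.

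**4. Other formulas at 30% vs 45%.** Colleges per arm under more lenient choices:

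| Variant | Colleges per arm |
|---|---|
| Three-group chi-square, 90% power | 21.2 |
| One-sided, 90% power | 18.5 |
| Both interventions pooled vs control, 90% power | 17.2 |
| Two-sided, 80% power | 17.1 |
| One-sided, 80% power | 13.4 |

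None gives 8.

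**5. Power with 8 colleges per arm.** Students per arm: 8 × 190 = 1520. Effective size: 1520 / 19.9 = 76.4. Standardised difference: 0.15 / √(0.4575 / 76.4) = 1.938.
- Normal: Φ(1.938 − 1.960) = 0.49.
- Noncentral t, 21 df (24 colleges, 3 arms): 0.46.
- Noncentral t, 14 df (the 16 colleges in one comparison): 0.44.

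At 150 students per college these are 0.49, 0.45 and 0.43; at 131 they are 0.48, 0.45 and 0.43. Larger colleges cannot help much: at ICC 0.1, eight colleges cap the effective size at 8 / 0.1 = 80 per arm, where normal-approximation power is 0.51.

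**6. What 8 colleges of 190 could detect at ICC 0.1, from a control rate of 30%.**

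| Intervention rate | Power, normal | Power, t (21 df) |
|---|---|---|
| 52% | 0.81 | 0.77 |
| 53% | 0.84 | 0.81 |
| 55% | 0.90 | 0.87 |
| 56% | 0.92 | 0.89 |
| 57% | 0.94 | 0.92 |

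**7. Power for 30% vs 45% by ICC, 8 colleges of 190.**

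| ICC | Power, normal | Power, t (21 df) |
|---|---|---|
| 0.01 | >0.99 | >0.99 |
| 0.02 | 0.98 | 0.97 |
| 0.03 | 0.92 | 0.89 |
| 0.05 | 0.76 | 0.72 |
| 0.10 | 0.49 | 0.46 |

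The ICC that gives 90% power is about 0.032 (normal) or just under 0.03 (t, 21 df).

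**8. Student totals.** 24 × 190 = 4560. The stated 3144 implies 3144 / 24 = 131 per college, and 3600 implies 3600 / 24 = 150.

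**9. A possible origin, not stated in the article.** The Sample Size section cites 21.5% coverage in 2023 as the basis for the 30%. For 21.5% vs 45%, the unpooled n is 10.507 × (0.215 × 0.785 + 0.2475) / 0.235² = 79.2 per arm. Then 79.2 × 19.9 / 190 = 8.3 colleges per arm, and 2 × 79 × 19.9 = 3144.2.

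**The case against.** Four things can be said for the plan.

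- **The ICC is described as conservative.** If the true ICC is about 0.03 or less, 8 colleges do reach 90% power. But 0.1 is the planning value from which the result is said to follow, and the article claims no smaller one. An analysis that explains part of the between-school variation could also help, but the calculation takes no credit for that.
- **The article concedes possible loss of power.** Study Limitations does so, but attributes it to rising coverage over time. It does not address a starting power near one half.
- **The totals are labelled approximate, and 190 is an average enrolment.** This softens the conflict over totals without explaining it. It does not affect the main point, since power barely moves between 131 and 190 students per college.
- **The sentence in Study Strengths gives no figure for power.** That stands. It only needs to agree with the corrected calculation.

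Three stronger readings are tempting, and the article supports none of them. A reader might infer from step 9 that the authors computed at 21.5%, counted two arms and later changed the control rate. The match is close, but the article names 30% as its hypothesis and shows no such calculation, so this remains conjecture. A reader might infer that the trial must recruit 69 colleges. The inputs imply 23 per arm, but restating the power or justifying another ICC would also remove the contradiction. Finally, a reader might assume that a null result will be reported as proof of no effect; the article commits to no such interpretation.

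**Conclusion.** The sample-size statement is wrong as written. Its own inputs lead to 23 colleges per arm, about three times the 8 planned. With 8, power per comparison with control is about 44-49%, depending on the approximation, against the stated 90%. No standard variant tried at 30% vs 45% closes the gap. The student totals of about 3144 and about 3600 agree neither with each other nor with 24 × 190 = 4560.

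This rests only on the article's stated rates, ICC, college size and two-sided 5% level. It assumes equal college sizes, full follow-up, no covariate gain and no adjustment for two comparisons with control. Splitting alpha to 0.025 would lower normal-approximation power to about 37%. How the figure of 8 arose is not established, and the conclusion does not depend on it.

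**What to change.** Redo the calculation in the Sample Size section so that inputs and result agree. For 24 colleges, there are two ways to do this:

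1. **Keep ICC 0.1.** State power of about 44-49% per comparison for 30% vs 45%. Give the detectable difference with the approximation named: 80% power at about 30% vs 52% (normal) or 53% (t, 21 df), and 90% power at about 30% vs 55% (normal) or 56-57% (t, 21 df).
2. **Justify a smaller ICC.** Support it with evidence and show a power table over 0.01-0.10, making clear that 90% power needs about 0.03 or lower. With so few colleges, the t-based column should appear beside the normal one.

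Use one student total in the Abstract and the Sample Size section, and explain any difference between enrolled and expected participating students. Bring the sample-size remark in Study Strengths into line with the corrected power.

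The change is to text only. The article expects a start in August 2026, with ethics approval still in progress, so there is time to make it. The one drawback is a less favourable stated power.

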### Recruitment

Our sample will include seventh-grade middle school students from randomly selected schools in Réunion Island, following approval from the school directors. These schools will be randomly assigned to 1 of the 3 groups in a 1:1:1 ratio using a randomization algorithm. All students attending the selected schools will be invited to participate in the study (Figure 2).

### Eligibility Criteria

Inclusion criteria are students in seventh-grade classes from middle schools in Réunion Island who are randomly selected and assigned to the study.

Exclusion criteria are students with parental opposition to participating.

### Intervention

#### Control Group

The control group will consist of 8 randomly assigned middle schools. These schools will follow the existing vaccination campaign, without any modifications, as implemented by the French government. As vaccination campaigns are coordinated by the local Regional Health Agency, they are relatively uniform across all middle schools in Réunion, ensuring standardization and internal validity. Parents will receive information materials and consent forms through their children. Both parents are invited to sign the written consent form, which the child will then submit to the school counselor or school nurse. The counselor or nurse will forward the forms to the vaccination teams assigned to the area. This allows the vaccination teams, in coordination with the education staff, to schedule their visit to the school on a specific day and bring the appropriate number of vaccine doses corresponding to the consent forms received. Vaccination teams typically visit each school twice a year to administer 2 vaccine doses 6 months apart, usually in December (year Y) and June (year Y+1).

A preintervention questionnaire will be administered to assess students’ baseline knowledge about HPV (T0). The questionnaire will be standardized, anonymous, and identical for all participants. It will be available on tablets, computers, or on paper, depending on availability. A postintervention knowledge assessment will be conducted 3 months later (T1) using a questionnaire identical to the preintervention one, to evaluate changes in the rate of correct responses before and after the vaccination campaign.

The standardized knowledge questionnaire was developed by the research team and will assess students’ knowledge of HPV epidemiology, complications, and prevention (including vaccination; Multimedia Appendix 1). Each question requires a response of “yes,” “no,” or “I don’t know.” The questionnaire consists of 11 questions.

Vaccination status will be collected using the French social security system after anonymization of social security numbers (T3).

#### Intervention Group: Ambassador Class (Peer Learning)

For each college randomized to this arm, 1 seventh-grade class will be randomly selected as the ambassador class. If a college has more than 5 seventh-grade classes, 2 ambassador classes will be designated (Figure 2). Students in the ambassador class will receive the intervention during a single class period.

This group will receive a 30-minute presentation on HPV delivered by a trained facilitator during class. The presentation will be standardized and consistent across all participating classes to minimize potential bias. Developed in advance by a team of experts, it will remain identical for all classes in this intervention arm. The presentation will cover key topics, including HPV, its epidemiology in France and Réunion Island, its benign and malignant sequelae, and preventive measures such as screening and vaccination. To assess students’ understanding of the material, they will complete a satisfaction questionnaire following the presentation.

The same preintervention (T0) and postintervention (T1) questionnaires used in the control group to assess HPV knowledge will be administered.

This arm, which integrates peer learning, will train “ambassador classes” on HPV prevention. In a second step, these students will disseminate the information to their peers in other seventh-grade classes within their middle school (T2). They will have the autonomy to choose the format for delivering the information during class (eg, games, presentations, films, posters, slideshows, comics [20]). Students who receive the information from their peers will also complete a satisfaction questionnaire. A field coordinator (a volunteer teacher) will be present during the training sessions to ensure that essential information is effectively conveyed and, if necessary, to supplement any important details that may have been omitted in the student-led presentations.

Vaccination status will be collected using the French social security system after anonymization of social security numbers (T3).

#### Intervention Group: Serious Game Cards

The intervention for this group will involve a card game modeled after an “unlock” serious game, specifically designed for this study to raise awareness about HPV. All seventh-grade classes in the randomized middle schools will participate in the game during a 1-hour class session. Sufficient sets of the card game will be provided to ensure that each student can actively participate. Middle school students will be supervised by a volunteer science teacher.

The game was designed to be played directly by students working in teams.

The game consists of 3 types of cards:

Yellow cards: feature fictional child characters expressing their own doubts about the HPV vaccine, as well as concerns raised by their parents.Blue cards: provide answers addressing the children’s doubts or fears.Green cards: respond specifically to the concerns expressed by parents.

First, the teacher reads the game instructions and mission order to the students for 5 minutes. A deck of cards is then distributed to groups of 3-4 students. According to the game rules, students must form a correct trio by matching 1 yellow card with 1 blue card and 1 green card (Figure 3). Students have 45 minutes to solve as many card trios as possible by finding the correct matches. Each correct answer represents 1 vaccinated child in their class and must be validated by the teacher. The final objective is to “vaccinate” as many children as possible.

**Figure 3 figure3:**
[figure not shown]
Serious game about HPV vaccination.

The intervention is grounded in a participatory communication approach that fosters active engagement among students. Children lead the game themselves, encouraging peer interaction and collaborative learning.

Children and parents were not involved in designing this game. However, the doubts featured on the yellow cards were derived from a study conducted a few years ago to identify barriers to HPV vaccination in schools [11]. A pilot evaluation of the game was carried out in 1 middle school, which helped identify areas for improvement and ensured smoother implementation.

At the end of the allotted time, teachers and students can debrief together to reinforce key concepts about HPV, and the teacher can answer any questions. The remaining 5 minutes of class time are allocated for students to complete the satisfaction questionnaire.

The same preintervention (T0) and postintervention (T1) questionnaires used in the control group to assess HPV knowledge will be administered.

In addition, students will complete a satisfaction questionnaire following the game, which will take a maximum of 5 minutes.

Vaccination status will be collected using the French social security system after anonymization of social security numbers (T3).

